**1. ABSTRACT**

In view of the low breastfeeding rates (BF) and practical sub-optimal complementary feeding in Brazil; the large number of adolescent mothers in our country; the presumed influence of grandmothers on feeding practices of their grandchildren; the fact that adolescent mothers who live with their mothers (maternal grandmothers of children) are considered to have an increased risk of inadequate feeding practices of their young children; and also the lack of intervention studies with adolescent mothers and grandmothers, it was conducted in the years 2006 to 2008, a randomized clinical trial to evaluate the efficacy of an intervention (six BF counseling sessions and healthy complementary feeding, carried out in the first four months of the child's life, the first in the maternity and the others in households) directed to adolescent mothers and grandmothers on exclusive breastfeeding prevalence (EBF) in the first six months of life and the BF prevalence and adoption of healthy complementary feeding and timely in the first year of life. Due to the favorable results of the intervention on all outcomes studied, it is intended, with this study, knowing the impact of the intervention on dietary habits and nutritional status of children in preschool age and brothers who are born after the intervention. For this, 252 children who were part of the clinical trial will be reassessed at age 4-6 years and younger siblings. Children in the intervention group will be compared with the control group regarding: anthropometric indicators (BMI, height), diet, adequacy of intake of macro and micronutrients as recommended for the age group (Dietary Reference Intakes - DRIs), the duration of BF (preschool for only), the duration of EBF and BF prevalences in the first year of life (only for younger siblings). To quantify the impact of the intervention in the various outcomes will be used Cox regression (hazard-ratio). In the analyzes, will be considered cohabitation with the grandmothers and other relevant variables. Our hypothesis is that the positive impact of the intervention acquired in the first year of life has positively reflected in anthropometric indicators and eating habits of children in preschool and younger siblings.

**2. INTRODUCTION**

The nutritional habits has undergone many changes, affecting mainly the nutritional status of individuals. Breastfeeding (BF) must attended the evolution of the human species in 99.9% of its existence. Despite being biologically determined, this practice, to be under the strong influence of socio-economic and cultural factors, with time has undergone a marked decline. The abandonment of breastfeeding showed, through time, to have harmful consequences for child health, such as high rates of mortality and malnutrition, and also long-term consequences, such as increased predisposition to chronic diseases, including obesity.

Several studies have indicated the BF and EBF as protective factors against overweight / obesity 1-3. Three meta-analyzes with observational studies found that the risk of obesity was lower (15-25%) in breastfed infants compared with those who received infant formula4.

In the UK, a cohort study evaluated the gain from birth to three years of age of 10,533 children and concluded that the initiation and duration of breastfeeding were significantly associated with weight gain in that period. Infants who did not receive breast milk had higher weight gain than those who were breastfed (z score coefficient: 0.06; 95% CI: 0.02 to 0.09) and those breastfed for less than four months compared with those who were breastfed for longer (z score coefficient: 0.05; 95% CI: 0.01 to 0.09). The authors concluded that initiate and prolong breastfeeding can reduce the excess weight in preschool age 5.

In Japan, a cross-sectional study of 448 preschoolers noted that the prevalence of overweight in children who had been exclusively breastfed was 3.8% and in formula-fed infants, 11.8%. However, the EBF until six months was not associated with significant reductions in overweight (OR: 0.70; 95% CI: 0.30 to 1.64) 6.

In Brazil, there are few studies related to the association between breastfeeding and overweight / obesity. Balaban et al.,7 conducted a cross-sectional study in the city of Recife with 409 children. The authors concluded that children who were breastfed for less than four months had a higher prevalence of overweight compared to those breastfed for longer. Another study conducted in São Paulo, also found a protective effect of breastfeeding against obesity. The authors concluded that children who were never breastfed were twice as likely to develop obesity8. And, also in São Paulo, Simon et al.9 found through sectional study that EBF for six months and BF for more than 24 months protected against overweight and obesity in a population of 566 children between 2 and 6 years old enrolled in private kindergarten schools.

According to some authors, the protection given to breastfeeding against overweight / obesity is related to the unique composition of human milk, reflecting on the process called metabolic imprinting. This process influence, for example, the number and / or size of adipocytes or inducing metabolic differentiation, occurring in a critical and specific period of development in which early food experiences have lasting effect10. Another latest theory is that adiponectin, a protein hormone produced by fat tissue and found in human milk in concentrations above the limit of leptin, would be related to metabolic activities including increased insulin sensitivity, metabolic control and suppression of inflammation, which could explain, at least partially, the protective effect of human milk against overweight / obesity11.

In the apparent protection of breastfeeding against overweight / obesity, includes the effect of the introduction of complementary foods in the diet of children. It has been demonstrated association between early consumption of these foods and obesity in childhood and adulthood12,13.

Despite evidence of the benefits of EBF, the BF and the healthy complementary feeding, the indicators of BF and complementary feeding in Brazil are sub-optimal, as shown by the II Breastfeeding Prevalence Research in Brazilian capitals and the Federal District held in 200814: median duration of EBF of 52 days with less than 10% of children being exclusively breastfed at six months; BF median duration of 11.2 months, with only 45.5% of children being breastfed for 12 months or more; early onset of complementary feeding, with a quarter of children between three and six months already receiving salty food and / or fruit, 9% consuming biscuits and snacks and almost half receiving other milk between four and six months of life, with 18% receiving this food in the first month of life.

The scientific literature has pointed out several factors related to the early termination of the EBF and BF and early introduction of complementary foods, including the low maternal age and cohabitation with the child's maternal grandmother15-23.

Studies in Canada17, the US24 and Norway16 suggest that adolescent mothers are particularly prone to introduce other foods early to the detriment of EBF. In Brazil, a study conducted in the State of São Paulo, involving 33,735 children, found that primiparous women younger than 20 years were 20% higher chance to abandon the EBF before four months15. Still in Brazil, Giugliani et al. identified the adolescent motherhood as one of the determinants for the interruption of EBF before six months (HR = 1.48, 95% CI= 1.01 to 2.17)25.

There is no doubt that grandmothers, in general, influence the eating habits of young children and can contribute to the success of hers daughters BF26. On the other hand, the literature has shown that some grandmothers had a different experience with their own children, and can recommend currently outdated practices such as early use of water, teas, and other milk solids / semi-solids in children under six months.

Some studies conducted in Brazil point to a possible negative influence of grandmothers on feeding their grandchildren in the first months of life. In Natal, Brazil, the prevalence of EBF was significantly lower in children with grandmothers present in the family group27. In Porto Alegre, a cohort study of 601 mother-infant pairs found that, regardless of maternal characteristics, only the fact that the maternal or paternal grandmother recommend the introduction of water and / or tea and another type of milk in the diet of baby significantly increased the risk of it not be breastfed exclusively until the end of the first month (OR = 2.22; 95% CI = 1.50 to 3.30 and OR = 1.83, 95% CI = 1,24- 2.71, when the maternal and paternal grandmothers, respectively, recommended water and / or tea and OR = 4.51, 95% CI 2.14 to 9.49 and OR = 1.86; 95% CI = 1, 1 to 3.42 when the maternal and paternal grandmothers, respectively, recommended another type of milk)19. Also in Porto Alegre, in another cohort, Giugliani et al. demonstrated that the introduction of water and tea was associated with cohabitation with the maternal grandmother (HR = 1.51; 95% CI 1:10 to 2:10)25.

Based on the knowledge described above and considering: low rates of BF and EBF and early onset of complementary foods in Brazil14; the large number of adolescent mothers in our country 28; the presumed influence of grandmothers on feeding practices of their grandchildren; the fact that adolescent mothers living together with their mothers (maternal grandmothers of children) are considered to have increased risk for inadequate eating habits early in life for their children; and also the lack of intervention studies with adolescent mothers and grandmothers, was conducted in the years 2006 to 2008, a randomized clinical trial to evaluate the efficacy of an intervention (six BF counseling sessions and complementary feeding made in the first four months of the child's life) designed for adolescent mothers and grandmothers in EBF rates in the first six months of life and in breastfeeding rates and adoption of healthy complementary feeding in the first year of life. The main results of this trial are summarized as follows:

- The intervention reduced the unnecessary use of water and / or teas in children breastfed for the first six months by 52% (HR = 0.48, 95% CI 0.31 to 0.76) when it was applied only to adolescent mothers. When the intervention included maternal grandmothers, the protection was 47% (HR = 0.53; CI 95% = 0.35-0.80); and postponed for 44 days the use of these liquids in the group where only the adolescents received the intervention (78 days, 95% CI 50.2 to 105.8 without intervention versus 122 days, 95% CI 107.6 to 136.3 with intervention) and 67 days in the group where the grandmothers were also included in the intervention (63 days, 95% CI 47.2 to 78.7 without intervention versus 130 days, 95% CI 113.4 to 146.6 with intervention29.
- The intervention increased the median duration of EBF in 67 days in the group that only adolescent mothers received the intervention (103 days; 95% CI = 82.4 to 123.5 with intervention versus 36 days; 95% CI = 21.5 to 50 5 without intervention) and 46 days in the group where the grandmothers were also included in the intervention (89 days, 95% CI 56.8 to 121.2 with intervention versus 43 days, 95% CI 29.9 to 56.1 without intervention); and reduced by 48% the EBF abandonment in the first half when applied only to adolescent mothers (HR = 0.52; 95% CI = 0.36-0.76) and 36% when included maternal grandmothers (HR = 0,64, 95% CI = 0.46-0.90)30.
- The probability of a child be fed with another milk remained lower over the first six months of life in the group receiving the intervention. The median age of introduction of other types of milk was 95 days (95% CI 78.7 to 111.3) in the control group and 153 days (95% CI 114.6 to 191.4) in the intervention group. Therefore, the intervention delayed in nearly two months the introduction of other milks31.
- The intervention had a positive impact on the early introduction of complementary foods. At four months, 41% (95% CI 32.8 to 49.2) of the control group were receiving complementary foods. This prevalence decreased to 22.8% (95% CI 15.9 to 29.7) in the intervention group. However, the six-month prevalence rates of children receiving complementary foods were similar in both groups: 88.4% (95% CI 82.9 to 93.9) for the control group and 87.1% (95% CI 81,4 to 92.8) in the intervention group31.
- The intervention had significant impact on BF rates only for the group that the grandmother did not live with the mother and the child. The proportion of children breastfed at 12 months in the intervention and control groups that did not cohabitate with her maternal grandmother was 38 and 62% respectively, setting a difference of 24 percentage points; in groups where there was cohabitation with her grandmother, this difference was 8% (41 versus 49%); the risk of weaning in the first 12 months was 49% lower in the group of adolescents who received the intervention and not lived with the grandmothers (HR = 0.51; 95% CI 0.30 to 0.85) and 26% lower the group in which the grandmothers participated in the intervention (HR = 0.74; 95% CI 0.47 to 1.16)32.
- The EBF, BF and complementary feeding indicators were similar in both control groups, indicating that cohabitation with maternal grandmothers did not significantly affect these indicators. However, the cohabitation of adolescent and child with her grandmother had a negative influence on the impact of the intervention29-32.

Given the concern about the increasing prevalence of overweight / obesity in preschool children and the positive results of multiple counseling sessions in BF and complementary feeding carried out in the first four months of the child's life, for adolescent mothers and grandmothers in the main child feeding indicators in the first year of life, we believe it is relevant to know the impact of this intervention on dietary habits and nutritional status of children in preschool and also of other children who were born after intervention. That was the motivation to carry out this study.

**3. AIM**

**3.1. General aim**

To evaluate the impact in the medium term, of multiple counseling sessions in BF and complementary feeding carried out in the first four months of the child's life, for adolescent mothers and grandmothers when these lived with her daughters on dietary habits and nutritional status children in preschool and younger siblings.

**3.2. Specific aim**

1. Compare anthropometric indicators of preschool and younger brothers of the experimental and control groups.
2. Compare eating habits of preschool and younger brothers of the experimental and control groups.
3. Compare adequacy of intake of macro and micronutrients as recommended for the age group (Dietary Reference Intakes - DRIs) age of preschool and younger brothers of the experimental and control groups.
4. Compare the total duration of breastfeeding of preschool children of the experimental and control groups.
5. Compare the EBF and BF indicators in younger siblings of preschoolers of the experimental and control groups.
6. Compare the performance of the ten steps of healthy eating for children over two years of preschool children in the intervention and control groups.
7. Compare the consumption of unhealthy foods of preschool and younger children in the intervention and control groups.

**4. HYPOTHESIS**

Our hypothesis is that the positive impact of the intervention in the EBF and BF indicators and the adoption of healthy complementary feeding in the first year of life has positively reflected in anthropometric indicators and eating habits of children in preschool and their younger siblings.

To test this hypothesis, children who participated in the first phase of the trial will be evaluated at age 4-7 years and younger siblings, when present, the main outcomes: BMI, height, eating habits and appropriate consumption of macro and micronutrients, as well as total time of BF of the children involved in the first phase of the trial and prevalence and patterns of breastfeeding and eating habits of younger siblings.

**4. METHODS**

This study is a continuation of a randomized clinical trial initiated in 2006 and will be conducted in the city of Porto Alegre, at the Centre for Clinical Research of the Porto Alegre University Hospital and / or families of households whose mothers, children and grandmothers were included in the clinical trial.

The population of this study includes 252 children (and their younger siblings), aged four and seven years, who participated in the clinical trial.

**5.1. Information about the first phase of clinical trial**

For sample size determination, the EpiInfo software was used with the following parameters: α = 5%; β = 20%; ratio between exposed and unexposed = 1: 1; prevalence of EBF in the first month in the group not exposed to the intervention = 56% (ALMEIDA, 1999); difference in the prevalence of EBF in the first month of the unexposed group and the group exposed to the intervention = 25 percentage points. Considering also the same difference between groups (25%) in reducing excess weight in the intervention group of preschool age (KOLETZKO, 2009), it was estimated minimum sample 48 mother-child pairs for each group. Added to this number 10% for losses and 20% for performing multiple regression analysis, totaling approximately 63 participants in each group.

Adolescent mothers, their infants and grandmothers were recruited in the rooming-in facility of the Porto Alegre University Hospital between May 2006 and January 2008, and followed in their homes to children reaching one year of age. Daily, including weekends, mothers were identified that met the following inclusion criteria: age under 20 years, living in the city of Porto Alegre, with healthy babies and birth weight equal to or greater than 2,500 g who had started breastfeeding. Mothers of twins and that, for mother or baby's problems could not stay in rooming and the adolescent mothers living with their mothers in law were not included in the study.

Once identified, mothers were classified into two groups: those who lived and not lived with their mothers (maternal grandmothers of the child). Next, by lottery, they were allocated to the control group (who did not receive the intervention) or the intervention group. In these, when mother and grandmother lived together, both were subjected to intervention; when not cohabiting, only the mother received the intervention. The inclusion of the latter group aimed to evaluate how much of the impact of the intervention could be attributed only to the adolescent mother. All mothers, regardless of the group to which they were allocated, received standard hospital care.

Data collection was performed at different times. In maternity ward, adolescent mothers and grandmothers, after agreeing to participate and signed the written informed consent, were interviewed separately to obtain sociodemographic data and aspects related to prenatal care, childbirth and experience prior to breastfeeding. Separate questionnaires were used for mothers and grandmothers. Information on the children's diets in the first six months of life were obtained monthly by telephone interview with the mother, or home visits in telephone contact impossibility. Interviewers were blind to the group to which they belonged mothers. To check the quality of information, were randomly selected 5% of mothers every month, which were submitted by the researcher coordinator of field, a second interview containing some key questions of follow-up questionnaire.

Intervention sessions occurred in the maternity ward and at home. In the maternity ward, occurred the first counseling session on breastfeeding according to the principles of the World Health Organization33, conducted by one of the team members formed by two nurses, a nutritionist and a pediatrician, all with extensive experience in BF, three consultants lactating by the International Board of lactation Consultant Examiners (IBLCE). Interventions in maternity ward were individual and performed separately for the mother and grandmother. In households, the advice was simultaneous.

In counseling sessions, professional, mother and grandmothers dialogued informally about various aspects related to breastfeeding - its importance and recommended duration; Factors that influence the production of milk; breastfeeding technique; pacifier use consequences; crying baby and communication - as well as specific questions for each mother and grandmother were clarified. The mothers were encouraged to breastfeed during the intervention, whenever possible, taking advantage of the opportunity to observe the feeding and guide as to positioning and latch.

As support material, flip charts specially designed for research were used containing information about breastfeeding and prevention and management of common problems. A handbook with similar content to the flipchart was distributed at the end of counseling at the hospital.

In households, mothers and grandmothers, when cohabiting, received sessions of reinforcement counseling when children completed 7, 15, 30, 60 and 120 days. At these sessions, discussed the difficulties faced by mothers and their management, as well as reinforced the messages passed in counseling at the hospital. After 120 days, the intervention also addressed complementary feeding, according to the Guia de Alimentação Para Crianças Brasileiras Menores de Dois Anos 34.

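### The sample-size paragraph counts a 25% difference in preschool excess weight as part of its 80% power basis, but the source it cites reports a 15-25% relative risk reduction for a different contrast

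*Protocol*

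**What the plan says.** Section 5.1 of the protocol holds its only sample-size statement. The design parameters are "α = 5%; β = 20%; ratio between exposed and unexposed = 1: 1". The first-phase outcome is defined fully: "prevalence of EBF in the first month in the group not exposed to the intervention = 56" per cent, with a difference of 25 percentage points. The paragraph then adds the second-phase weight outcome: "Considering also the same difference between groups (25%) in reducing excess weight in the intervention group of preschool age", citing a 2009 source. From these it derives 48 mother-child pairs per group, adds 10% for losses and 20% for multiple regression, and reaches about 63 per group. No control prevalence of excess weight is given.

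The 2009 source is entry 4 in the reference list. The Introduction summarises it as three meta-analyses of observational studies in which "the risk of obesity was lower (15-25%) in breastfed infants compared with those who received infant" formula.

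The second phase takes the 252 children of the trial as its population (Methods). The Hypothesis section names BMI among the main outcomes, and section 5.2 plans to compare mean z scores and nutritional classification between the arms.

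**The concern.** The same source is used for two different quantities. The Introduction treats 25% as the upper end of a relative risk reduction. Section 5.1 calls it the same difference as the 25 percentage points for exclusive breastfeeding, which makes it absolute.

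The contrast changes too. The source compares breastfed with formula-fed infants. The trial compares counselled with uncounselled mothers, and section 5.1 made having started breastfeeding an inclusion criterion for both arms. Nothing in the protocol justifies carrying the feeding-type effect over to the counselling contrast at full size.

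What is at stake is how the weight result will be read. The paragraph tells the reader that excess weight at preschool age was part of the basis for an 80% power calculation. A non-significant weight comparison could then be taken as evidence of no medium-term effect, although the study had little chance of detecting an effect of the cited size.

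**Working it through.** **Inputs from the protocol.** α = 5%, β = 20%, ratio 1:1, exclusive breastfeeding 56% versus 81%, 48 per group, about 63 after inflation (section 5.1); 252 children (Methods); relative reduction 15-25% (Introduction). As 252 = 4 × 63, pooling the two cohabitation strata gives 126 per arm before losses.

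**Assumptions.** Two-sided testing, in line with the planned 95% intervals and p < 0.05. Control prevalence of excess weight 10-50%, since none is stated for this population.

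**Formula.** Two proportions, pooled variance under the null, with p̄ = (p1 + p2)/2:

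power = Φ{ [ |p1 − p2| − 1.96·√(2·p̄(1 − p̄)/n) ] / √[ (p1(1 − p1) + p2(1 − p2))/n ] }

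**Step 1: the plan's own figure.** For 56% versus 81% this formula needs 54 per group, not 48; two-sided power is 76% at 48 and 86% at 63. Other two-sided variants give 51 to 61. One-sided with continuity correction gives 50, close to 48, but no one-sided test is stated. The inflation step does reproduce: 48 × 1.3 = 62.4 and 48 × 1.1 × 1.2 = 63.4. The gap between 48 and 54 is small and separate from this point. The weight half of the calculation cannot be reproduced at all without a control prevalence.

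**Step 2: the clause read as 25 percentage points.**

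| Control prevalence (assumed) | Power, 48 per group | Power, 63 per group |
|---|---|---|
| 26% | 96% | 99% |
| 30% | 91% | 97% |
| 40% | 79% | 89% |
| 50% | 72% | 83% |

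On this reading the size is adequate at 63 per group, but the source does not report such an effect. If control prevalence were below 25%, a fall of 25 points could not occur.

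**Step 3: the cited effect, a 25% relative reduction (p2 = 0.75·p1).** Worked example at p1 = 0.30 and n = 126:
- p2 = 0.225, difference 0.075, p̄ = 0.2625
- 1.96·√(2 × 0.2625 × 0.7375/126) = 0.1086
- √[(0.2100 + 0.1744)/126] = 0.0552
- power = Φ[(0.075 − 0.1086)/0.0552] = Φ(−0.61) = 27%

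| Control prevalence (assumed) | Difference, points | Power, 63 per group | Power, 126 per arm | n per group for 80% |
|---|---|---|---|---|
| 10% | 2.5 | 7% | 10% | 2,005 |
| 20% | 5.0 | 11% | 18% | 906 |
| 30% | 7.5 | 16% | 27% | 540 |
| 40% | 10.0 | 22% | 38% | 356 |
| 50% | 12.5 | 29% | 52% | 247 |

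To reach 80% power, control prevalence would have to be about 86% at 63 per group or 69% at 126 per arm.

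**Step 4: the lower end of the cited range, a 15% relative reduction.** Power at 126 per arm is 6% at a prevalence of 10% and 22% at 50%.

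**Step 5: what 126 per arm can detect with 80% power.**
- Excess weight from an assumed 30%: 30% versus 15.3%, a difference of about 15 points.
- Mean BMI z: (1.96 + 0.84) × √(2/126) = 0.35 SD. At 63 per group it is 0.50 SD.

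**The case against.** The best defence is that section 5.1 reports a first-phase calculation whose only complete inputs concern exclusive breastfeeding, that the cohort is already fixed, and that excess weight is one of several outcomes, with mean z scores compared as well. All of this is true, and it limits the severity: no enrolment, outcome or analysis would change. It does not remove the clause, which concerns a second-phase outcome and stands in the protocol's only sample-size statement.

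A reader might also infer more than the documents support:

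- **That the study has no power for weight at all.** Step 2 shows good power for a genuine 25-point fall. A 50% relative reduction from an assumed 30% would have 82% power at 126 per arm. The shortfall is for the cited effect.
- **That a 25-point fall is impossible here.** The Introduction quotes "exclusively breastfed was 3.8% and in formula-fed infants, 11.8" per cent, but for Japanese preschoolers. No prevalence is given for Porto Alegre, so the impossibility is conditional on a control prevalence below 25%.
- **That the z coefficients in the Introduction are a benchmark for BMI z.** The figure "z score coefficient: 0.06; 95% CI: 0.02 to 0.09" is for weight gain from birth to three years, a different outcome at a different age.
- **That the expected difference has a low ceiling because counselling shifted breastfeeding at 12 months by only 8 to 24 points.** Any such ceiling needs an assumed prevalence and a route through breastfeeding alone. The Hypothesis section also names healthy complementary feeding as a route.
- **That a 2009 source is an error because recruitment ran "between May 2006 and January 2008".** A follow-up protocol may cite later literature. The date adds nothing to the mismatch.

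**Conclusion.** The point holds as an unsupported effect assumption and should be fixed; it does not threaten the study. Section 5.1 turns a 15-25% relative reduction between feeding types into a 25% difference between trial arms alongside an absolute 25 points, and attaches 80% power to it. Under either reading the claim fails: 25 points is not what the source reports, and a 25% relative reduction is far out of reach of 48 to 63 per group. Even with all 252 children and no losses, power for the cited effect stays at or below 52%.

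The exact shortfall depends on the assumed control prevalence, on two-sided testing and on equal arms of 126. The conclusion does not depend on which prevalence between 10% and 50% is chosen. Losses to follow-up would lower these figures, as would any weakening of the effect because both arms had started breastfeeding.

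**What to change.** In section 5.1:

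1. Delete the excess-weight clause and its citation, so that the calculation rests on exclusive breastfeeding alone.
2. State that the second-phase sample is fixed by first-phase enrolment and that no 80% power is claimed for excess weight.
3. Give the detectable difference with its assumptions: with 126 per arm, two-sided 5% and 80% power, about 15 percentage points in excess weight from an assumed 30%, and about 0.35 SD in BMI z.
4. Restate both figures for the number of children actually re-assessed.

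If the sponsor prefers to keep an effect assumption for excess weight, the text should say whether it is absolute or relative, give the control prevalence, and explain why it applies to counselled versus uncounselled mothers.

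The cost is protocol wording and a less favourable power statement. No extra participants, visits or analyses are needed.
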